## Abstract

**Background:**

The NHS abdominal aortic aneurysm (AAA) screening programme (NAAASP) is both clinically and economically effective. One of the main determinants of this effectiveness is disease prevalence. AAA prevalence is decreasing over time, steadily reducing the efficiency of the current NAAASP screening policy. One alternative to whole population screening is targeted screening of high-risk groups. Whether this would detect a clinically and publicly acceptable proportion of disease, and whether it would improve cost-effectiveness are unknown. The aim of this research is to estimate the clinical outcomes and cost-effectiveness of targeted AAA screening.

**Methods:**

Rather than conducting an expensive and time-consuming randomized trial to directly test targeted screening, we will undertake in-silico trials of targeted AAA screening. To determine success criteria for in-silico trials, the ethics and issues around the acceptability of targeted screening will first be explored through focus groups and interviews. A qualitative evidence synthesis to identify issues associated with targeted screening will be used to establish themes and topic guides. To perform the in-silico trials, individual men’s outcomes from the NAAASP (2013–2024, ≈ 2,500,000 men, ≈ 1% with AAA) will be linked to primary care data from the Clinical Practice Research Datalink (CPRD) (20% overlap of records). Risk factors for AAA will be identified by developing a risk prediction model and used as targeted screening criteria in in-silico trials, with diagnostic accuracy as the primary outcome. A discrete event simulation model will be adopted to extrapolate the trial findings beyond the observed period. We will estimate the clinical and cost-effectiveness of targeted screening compared with the current whole population screening strategy. Data linkage will be undertaken under Health Research Authority Confidentiality Advisory Group (Section 251) approval. Linked data will be effectively anonymised. Participants in the qualitative substudy will provide informed consent for participation.

**Discussion:**

We expect this project to have a direct and significant impact on NHS, UK and worldwide AAA screening policies. The study findings will be submitted for publication in peer-reviewed journals and presented at scientific meetings.

## Background

Abdominal aortic aneurysm (AAA) is a significant cause of mortality and morbidity. In England and Wales each year AAA rupture causes more than 3,000 deaths and over 6,000 patients undergo surgical AAA repair to prevent rupture [1,2]. The MASS trial of AAA screening, the key study on which current AAA screening practices are based, demonstrated a 52% reduction in AAA-related mortality in men screened for AAA [3] resulting in the introduction of screening for men aged 65 across the UK and elsewhere [4]. Further trials performed since the MASS trial have confirmed the long-term effectiveness of screening in reducing the risk of death from ruptured AAA and an additional benefit in terms of reducing all-cause mortality in men who attend screening [5].

The NHS AAA Screening Programme (NAAASP), which is the biggest provider of AAA screening in the UK, invites all men in the year of their 65^th^ birthday for a one-off ultrasound scan to screen for AAA. The majority of men screened for AAA do not have an aneurysm (approximately 1% in 2018 [6]); therefore, a significant proportion of the cost of screening is spent on screening those men who do not have the disease. Unnecessary screening of healthy individuals has both considerable financial implications and negative psychological effects [7].

AAA prevalence is the key determinant of screening cost-effectiveness. AAA prevalence in NAAASP is lower than that in the MASS trial. Screening men for AAA is cost-effective at current disease prevalence [8], however prevalence is reducing over time [9] (Table 1). As disease prevalence falls over time, screening will become less and less cost-effective. Ultimately this may result in de-commissioning of the programme and places those men with occult AAA at risk of death from AAA rupture.

**Table 1 pone.0327856.t001:** Reducing prevalence of AAA over time in the NHS AAA Screening programme between years 2013 and 2023.

Screening year:	2013/ 2014	2014/ 2015	2015/ 2016	2016/ 2017	2017/ 2018	2018/ 2019	2019/ 2020	2020/ 2021	2021/ 2022	2022/ 2023
**Men invited for screening:**	300,889	293,779	284,583	281,575	282,583	292,629	288,429	210,800	274,800	314,900
**Men attending for screening:**	235,409	233,426	227,543	223,371	222,887	237,416	222,177	164,002	217,092	254,439
**Attendance:**	78.24%	79.46%	79.96%	79.33%	78.87%	81.13%	77.03%	77.80%	79.00%	80.80%
**Men with AAA (>3.0 cm):**	2,941	2,773	2,549	2,387	2,232	2,309	2,033	1,542	1794	1,942
**AAA prevalence:**	**1.25%**	**1.19%**	**1.12%**	**1.07%**	**1.00%**	**0.97%**	**0.92%**	**0.94%**	**0.83%**	**0.76%**

The critical threshold for cost-effectiveness of AAA screening is a disease prevalence in the region of 0.35%−0.55% amongst those screened [5,10]. Whilst current prevalence is higher than this estimate at just under 1%, the falling AAA prevalence in NAAASP suggests that AAA screening may become unviable for the NHS within the next 10–15 years. In addition, studies highlighting the risks around AAA screening, such as overdiagnosis suggest that screening may be causing more harm than benefit [11,12], also contribute to the clinical argument against AAA screening. Therefore, it is important to investigate alternative screening strategies now, well before prevalence falls to a level where screening is ineffective on economic grounds alone.

Targeted AAA screening has the potential to improve cost-effectiveness and ensure the longevity of the AAA screening programme but needs to be tested. Any targeted screening strategy is likely to be based, at least in part, on AAA risk factors such as smoking. This approach has been utilized in the recent United States Preventative Services Taskforce (USPSTF) recommendation to only offer AAA screening to men with a history of smoking, stating that offering AAA screening to men who have not smoked is only of marginal net benefit and should not be routinely offered [13].

Targeted AAA screening is unlikely to detect the same proportion of AAAs as a whole population screening strategy. This means that some men with AAA who would have been offered screening in a whole population screening programme will not be offered screening and will be at risk of fatal AAA rupture. Socio-economic deprivation affects AAA screening uptake [14]. There is lower uptake among men living in deprived areas, precisely the areas in which AAA is more prevalent [15]. There is therefore the potential for stigmatisation, inequity and loss of justice with targeted screening. Therefore, the public acceptability of, and ethical issues raised by, targeted screening require exploration.

### Aims and objectives

This study aims to determine the clinical and cost-effectiveness of targeted AAA screening. Rather than conduct an expensive and long randomized trial, we propose to use a statistical modelling approach using real-world screening data to investigate targeted AAA screening. We will use the outcome and risk factor data to re-parameterise an established discrete event simulation statistical model of AAA screening to determine the clinical and cost-effectiveness of targeted AAA screening. Alongside this, we will also conduct a qualitative evidence synthesis review and focus group discussions to understand the ethical aspects and public acceptability of targeted screening. This will be used to set the success criteria for the quantitative analyses and frame our overall project results.

## Methods

### Study design

In this research to undertake a quantitative analysis of targeted AAA screening we will link individual patient screening outcome data from NAAASP to individual men’s primary care records available in the Clinical Practice Research Datalink (CPRD). This dataset will be used to determine the clinical outcomes of targeted AAA screening strategies had these been used. An established statistical model of AAA screening will be used and modified to compare the long-term harms, benefits, clinical effectiveness and cost effectiveness of targeted screening with the current population screening strategy.

This research will be conducted in four separate work packages:

Work package 1: Linkage of 2013–2024 NAAASP individual patient screening outcome data with primary care records from the CPRD and dataset cleaning/processing.

Work package 2: Identification/confirmation of AAA risk factors for screen-detected AAA in primary care records. Establishment of hypothetical targeted screening strategies and building a primary care risk prediction model for screen-detected AAA.

Work package 3: In-silico diagnostic accuracy trials of the hypothetical targeted screening strategies. Update an established discrete event simulation model of AAA screening. Use the outputs from the in-silico trials as new model parameters to estimate long-term changes in benefits, harms and cost-effectiveness of targeted screening vs whole population screening.

Work package 4: A qualitative study of the ethics and acceptability of targeted screening for AAA running alongside work packages 1–3. Consisting of a qualitative evidence synthesis and focus groups including men with men who benefited, or will benefit for the screening, and members of the public.

### Work package 1 (WP1)

WP1 will involve the linkage of individual men’s data from the NAAASP with individual primary care records (Fig 1). The linked dataset will be prepared for analysis, including the conversion of coded primary care data into clinically meaningful research-ready data.

**Fig 1 pone.0327856.g001:**
[figure not shown]
Data flow diagram for data linkage between NAAASP and CPRD. NHSE – NHS England, NECSWS – NEC software solutions, SCWDSCRO – South Central & West Data Services for Commissioners Regional Office, CPRD – Clinical Practice Research Datalink, EMIS/Vision – GP software from where data derives, CAG – health research authority confidentiality advisory group.

Data from the NAAASP will cover an eleven-year period from 2013 to 2024, thus we expect to have screening records for over 2,500,000 men invited for screening and over 25,000 men with AAAs. Primary care data will be obtained from the Clinical Practice Research Datalink (CPRD). CPRD is a database of anonymised primary care medical records covering over ~19 million patients from 1927 different UK GP practices [16–19]. Coding of clinical events in CPRD has been both technically and clinically validated [20–26]. We estimate that at least 20% of men invited for screening between 2013 and 2024 will be currently registered with GP practices contributing to CPRD.

We will undertake data linkage using the CPRD’s established pathway and patient level data-flow model for non-standard linkages. For this study both CPRD Aurum and CPRD GOLD datasets will be extracted.

The linkage will be conducted as follows (numbers in brackets refer to the numbers contained within Fig 1); (1) CPRD will instruct GP software suppliers, EMIS and Vision, to share NHS numbers and GP software (EMIS/Vision) patient pseudonyms for CPRD contributing practices with NHSE (the CPRD cohort file). (2) NHSE will share the CPRD cohort file with the South Central & West Data Services for Commissioners Regional Office (SCWDSCRO). This is an organisation within NHSE which will carry out linkage itself. (3) NAAASP via their software provider NEC Software Solutions will extract data from the NAAASP database according to a predefined data specification. (4) NAAASP will then share this extract file with SCWDSCRO. (5) SCWDSCRO will link the CPRD cohort file and NAAASP extract by NHS number, filtering and removing those men not within the CPRD cohort file. CPRD identifiers (the GP software patient pseudonyms) are added to the remaining NAAASP records. A new pseudonym is generated for each individual and the NHS numbers are stripped from the dataset. (6) This datafile is passed to CPRD. (7a) CPRD will use the GP software pseudonyms to add the CPRD patient pseudonyms to the dataset and then remove these GP software pseudonyms. (7b) CPRD patient pseudonyms are used to add the CPRD data which is added to the dataset. (7c) The whole dataset is then re-pseudonymised by creation of a new CPRD patient ID that is study specific and removal of all other pseudonym IDs except the study pseudonyms and newly generates study specific CPRD patient IDs. (8) This dataset will contain the CPRD and NAAASP linked data and is passed onto the University of Leicester. (9) University of Leicester perform study analysis.

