In-silico trials will then be run using the full range of targeted screening strategies determined in work package 2. Significant risk factors (such as smoking) will be examined as criteria for screening, both in isolation and in combination. The primary outcome for these in-silico trials will be diagnostic effectiveness (sensitivity and specificity, positive and negative predicative values, likelihood ratio, diagnostic odds ratio and area under the receiver-operator characteristic curve). Secondary outcomes will be those required to re-parameterise the DES model (re-invitations, attendance, non-visualisation, AAA size distribution at screening, AAA prevalence at screening and proportion of AAAs detected). For each screening strategy, individuals will be categorized into invited and non-invited groups. In each of these groups, the actual screening outcomes will be known and using the true detection rate the overall proportional detection rate for each hypothesized screening strategy can be calculated.

The trial outputs from each targeted screening scenario examined will be compared for their effect on long-term clinical and cost-effectiveness. Absolute numbers of clinical events for the varying screening scenarios can be calculated using the DES model and used to compare clinical outcomes using the reference case scenario of whole-population invitation for screening as a comparator. Clinical results will be presented as changes to the number of clinical events, principally proportional AAA detection and AAA mortality but including the effect of quality-adjusted life years. Outcomes will be presented as the incremental cost per quality adjusted life gained and incremental net monetary benefit (INMB) between targeted screening and whole population screening. Sensitivity analyses will be conducted to explore the key assumptions used in the model; the effect of varying the methods for calculating smoking status, hypertension and hyperlipidaemia will be examined as well as additional sensitivity analyses for coding variations in any strong predictors of AAA identified in the risk prediction modelling exercise. Additional analyses relating to the management and delivery of both AAA screening and vascular surgical services will be considered on a case-by-case basis.

### Medical ethics work package 4

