### Sample size calculation

Allowing for a minimum of 20% data availability in CPRD, linked data will be available for just over 500,000 men, with over 5,000 AAA cases. We expect our most basic model of targeted screening based on smoking status alone to have a sensitivity for AAA detection of between 45% and 85% [29,30]. Our sample size of 5,000 AAA cases has adequate power to estimate sensitivities of 70% and above with a marginal error of +/- 1.5% and sensitivities of 75% and above with a marginal error of +/- 1.25% (Hajian- Tilaki method [31], α = 0.05). To develop an overall risk stratification model using primary care data (work package 2), having 5,000 men with AAA (events), we have an adequate sample size to build and validate a model with over 20 predictor variables (based on a 4:1 training:testing split) [27,28]. Recognizing that events-per-variable (EPV) thresholds have limitations and can be misleading as a sole basis for determining sample size, we have used more contemporary method of sample size estimation based on the 4-step method of sample size prediction by Riley et al [32]. Accordingly, the study will have sufficient data for the development, internal validation, and testing of the proposed risk stratification model.

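### The 2.5 million men labelled as invited fit the number screened, and "over 25,000" AAAs and "over 5,000" linked cases sit about 2% above what Table 1 supports

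*Protocol article*

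**What the plan says.** Work package 1 (text under Fig 1) sets the period: "Data from the NAAASP will cover an eleven-year period from 2013 to 2024". It then says "we expect to have screening records for over 2,500,000 men invited for screening and over 25,000 men with AAAs", and takes the CPRD overlap of at least 20% as a share of the men invited. The abstract gives the same total without the word invited: "2,500,000 men, ≈ 1% with AAA". The section on sample size carries the chain forward at the 20% minimum: "linked data will be available for just over 500,000 men, with over 5,000 AAA cases". From 5,000 cases it claims margins of ±1.5 points for sensitivities of 70% and above, and ±1.25 points for 75% and above, at α = 0.05.

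Table 1 in the Background has separate rows for "Men invited for screening" and "Men attending for screening", for the ten screening years 2013/14 to 2022/23. In every year its prevalence row equals AAAs divided by attenders.

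Work package 3 sorts men into those whom a targeted strategy would and would not invite, and says: "In each of these groups, the actual screening outcomes will be known".

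**The concern.** Two things look wrong in the stated sample. First, a total described as men invited is paired with an AAA count at a ratio of 1%, which in Table 1 is the rate among attenders. The reader cannot tell whether the 500,000 linked men are invited men or scanned men. Second, the two case counts are worded as exceeding 25,000 and 5,000, while Table 1 shows AAA numbers falling over the decade.

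The number of AAA cases underlies every precision figure in the sample size section and its model-development claim, so it should follow from the document's own table. The invited/screened distinction also matters in Work package 3. A man who was invited but never scanned has no AAA status, so he cannot count as a true or false positive or negative.

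**Working it through.** **The plan's own chain.** 2,500,000 × 1% = 25,000 AAAs; × 20% = 5,000 cases in 500,000 linked men. The stated figures reproduce from this chain.

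**Table 1, ten-year sums (2013/14 to 2022/23).**
- Invited: 2,824,967
- Attended: 2,237,762
- AAAs: 2,941 + 2,773 + 2,549 + 2,387 + 2,232 + 2,309 + 2,033 + 1,542 + 1,794 + 1,942 = 22,502
- AAAs per attender: 22,502 / 2,237,762 = 1.006%
- AAAs per man invited: 22,502 / 2,824,967 = 0.797%
- Invited but not attending: (2,824,967 − 2,237,762) / 2,824,967 = 20.8%

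**Eleventh year.** 2023/24 is not in Table 1. Assume it equals 2022/23 (314,900 invited, 254,439 attended, 1,942 AAAs).

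| | Eleven years | × 20% |
|---|---|---|
| Invited | 3,139,867 | 627,973 |
| Attended | 2,492,201 | 498,440 |
| AAAs | 24,444 | 4,889 |

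The stated 2.5 million is within 0.3% of the attenders. The number invited is 25.6% above it.

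**Case counts.** 24,444 is 2.2% below 25,000, and 4,889 is 2.2% below 5,000. Passing 25,000 needs more than 25,000 − 22,502 = 2,498 AAAs in 2023/24, about 29% above the 1,942 of 2022/23. The last year at that level was 2015/16 (2,549), and the last two years gave 1,794 and 1,942. Range for the eleventh year:
- 1,794 AAAs: (22,502 + 1,794) × 0.2 = 4,859 linked cases
- 2,309 AAAs: (22,502 + 2,309) × 0.2 = 4,962 linked cases

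**Precision.** The half-width is d = 1.96 × √(p(1 − p)/n), with a two-sided interval assumed.

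| n | p = 70% | p = 75% |
|---|---|---|
| 5,000 (stated) | ±1.27 points | ±1.20 points |
| 4,889 | ±1.28 points | ±1.21 points |
| Target | ±1.5 points | ±1.25 points |

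Cases needed, n = 1.96² × p(1 − p)/d²:
- 70% ± 1.5 points: 3,586
- 75% ± 1.25 points: 4,610

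Room for unusable records at the tighter target: (4,889 − 4,610) / 4,889 = 5.7%. From 5,000 cases it would be (5,000 − 4,610) / 5,000 = 7.8%.

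**Work package 3.** Linked invited men without attendance: 627,973 − 498,440 = 129,533, about 130,000. They would fall into both the invited and the non-invited group of any targeted strategy. Known AAA cases all come from scanned men. The choice of denominator therefore bears on specificity, the predictive values and prevalence, where unscanned men could be counted as disease-free.

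**The case against.** The strongest reply is that this is a labelling slip with no effect on the design. Much of that stands.

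- More than 2.5 million invited is true as a lower bound: Table 1 already shows 2.82 million in ten years.
- The overlap is given as a minimum. At 5,000 / 24,444 = 20.5% overlap the linked count would reach 5,000, so the shortfall applies at the stated floor.
- 2023/24 is an assumption here, not a tabulated figure.
- Both precision targets hold at 4,889 cases. The documents give no rate of unusable records, and the room would be limited even at 5,000.
- Work package 3 already lists attendance, non-visualisation and prevalence at screening as separate model inputs. Screening outcomes could be read to include recorded non-attendance.

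Three stronger conclusions are tempting, and the documents do not support them.

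- A reader might infer that the mixed denominator causes the case shortfall. It does not: the AAA count is 24,444 whichever denominator is used. The gap arises because exceeding 25,000 is optimistic while prevalence falls.
- A reader might take 2.5 million literally as the number invited, get 2,500,000 × 0.797% × 20% ≈ 3,983 cases and ±1.34 points at 75%, and conclude that the target fails. Table 1 rules this out, because more men than that were invited in ten years alone.
- A reader might fear that prevalence at screening will be understated by about a fifth. Nothing says it will be divided by men invited. Table 1 uses attenders, and the Background discusses the cost-effectiveness threshold among those screened.

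What the reply does not remove is that the text pairs an invited total with an attender rate, states case counts above what its table supports at the stated floor, and describes outcomes as known for groups that contain unscanned men.

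**Conclusion.** Minor, but wrong as written. The 2.5 million and 500,000 fit men screened, not men invited; the invited figures are about 3.14 million and 628,000. As a separate matter, the AAA counts are about 2% too high at the 20% floor: about 24,400 in total and 4,890 linked, or 4,860 to 4,960 linked if 2023/24 brings 1,794 to 2,309 cases. The stated precision survives, with about 6% of linked cases to spare at the ±1.25-point target. The Work package 3 statement is too broad, since about 21% of invited men did not attend.

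The eleven-year totals rest on 2023/24 resembling recent years, and the linked counts on exactly 20% overlap. The denominator mismatch rests on neither: it is visible in the ten tabulated years. No bias in results and no missed precision target has been shown.

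**What to change.** - **Work package 1 and Sample size calculation:** label the 2.5 million and 500,000 as men screened, or give both bases (about 3.1 million invited and 628,000 linked invited; about 2.5 million screened and 498,000 linked screened). Replace the two case counts by about 24,400 AAAs and about 4,900 linked cases, and state the assumption for 2023/24.
- **Sample size calculation:** restate the margins on about 4,900 cases (±1.28 points at 70%, ±1.21 at 75%). Give 4,610 usable cases as the floor for the ±1.25-point margin.
- **Work package 3:** correct the statement that outcomes will be known. Say that sensitivity, specificity, predictive values and prevalence at screening are computed among men with a scan result. Keep attendance on the invited denominator, as a separate input as already listed.

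The cost is wording and a short recalculation. The data request and the design do not change, and the stated case number becomes slightly less favourable.
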